### Ethical approval and informed consent

This observational study was approved by the Belgian Privacy Commission and by the Ethics committee of the Belgian Universities - Université Catholique de Louvain and Katholieke Universiteit Leuven with dossier number B40320108337. A formal procedure was implemented so that caregivers could fill out the questionnaires on a secured website.

For this study, older persons are asked to sign an informed consent agreement. In case they are not capable of signing this document, a family member or another legal representative will sign it on their behalf, as stipulated by Belgian law [21]. Clients do not undergo the intervention because of the research. The research however evaluates the effects of the intervention. Clients have the right not to participate in the research and they may withdraw their consent at any time. In that case, all data for this person is removed. Their consent or refusal to consent does not affect their participation in the intervention.

All data are anonymized and analyzed according to the rules of the Belgian Privacy Commission [22].

### Research questions

The aim of the study is to answer the following research questions:

1. Do characteristics of populations differ between projects?

2. Which types of projects are associated with less decrease of the functional and cognitive performance of frail older persons?

3. Which types of projects contribute to a better quality of life of frail older persons?

4. Which types of projects are associated with a decreased risk of institutionalization of frail older persons?

5. Is the interRAI Maple scale a good predictor of institutionalization in our study?

#### Selection of Variables

A previous systematic review identified the variables most frequently used in the evaluation of interventions aiming at maintaining frail older persons at home [14]. In our study, variables from the interRAI Home Care instrument which correspond to these identified variables will be used in the evaluation of interventions [23].

For data without any correspondence with the InterRAI instruments, other tools have been selected by a consensus amongst experts and according to their international validity. These complementary tools are the WHOQoL-8 and Zarit Burden scale (12-item) [24-26].

#### interRAI HC instrument

The interRAI HC instrument is an internationally validated instrument consisting of several domains such as cognitive functioning, ADL, social and psychological wellbeing, health status, environmental characteristics, etc. The use of a comprehensive geriatric assessment such as the interRAI HC is essential for this study in order to have an in-depth view of the client’s health and functional status [27-29]. The follow up of these characteristics will give insight in the evolution of the client’s situation and will enable researchers to show the effect of innovation projects. In the study we use the validated Belgian version of this instrument named BelRAI HC.

### WHO-QOL-8

The WHO defines Quality of Life as “individuals’ perception of their position in life in the context of the culture and value systems in which they live and in relation to their goals, expectations, standards and concerns” (24). The WHO-QOL-8 scale measures the perceived overall quality of life of the clients. It is derived from the WHO-QOL-Bref and contains each of the domains: physical and psychological health, social relations and environment [30,31]. It is currently used as an instrument in the WHO’s SAGE Survey [32]. This scale was designed for use where researchers need a short and concise instrument to measure quality of life. It is a self report instrument, so it has to be filled out by the clients themselves.

### Zarit Burden Interview 12 (ZBI-12)

In the international literature caregiver burden is perceived as a multidimensional response to stressors associated with care giving. These stressors may be physical, psychological, emotional, social and financial [33-35]. In this research we use a shorter version of the original 22-item scale Zarit Burden Interview. This scale contains 12 items with a score from 0 to 4. The total score can vary from 0 to 48 and the higher the total score, the higher the caregiver burden. The short form was chosen, in order not to put a heavier weight on the burden of the caregiver and to increase the response rate.

### Data collection

Professional caregivers are asked to fill out the interRAI Home Care instrument. Clients fill out the WHO-QOL-8 and the main informal caregivers complete the ZBI-12. These questionnaires are filled out at inclusion of the frail older person in the project (baseline), at exit from the project and 6 months after baseline. Additionally, if clients stay longer than 6 months in the project, caregivers have to do a follow-up every 6 months until the moment clients leave the project. Follow-up of clients happens from March 2011 until July 2013. A client follow-up period will vary between 6 to 36 months. Criteria to exit the cohort will be institutionalization longer than 3 months and death. Follow up will also end for clients who leave the projects.

Professional caregivers are instructed on how to fill out the questionnaires during a 2-day training and a follow up training of 1 day. They fill out the interRAI HC based on observation and on interview of the older person and of the main informal caregiver.

The interRAI-data will be linked with data from the national database IMA (Inter-mutuality Agency). This database contains data on national health service consumption reimbursed by NIHDI such as medication use, hospital days, medical, nursing and physical therapy use, etc. This data will be added to the analysis for the clients in the projects.

The “permanent sample” of people over 65 extracted from IMA database will also serve as a control group for our study population. By using this database we will be able to compare older persons who are benefiting from the innovative projects with older persons who are not benefiting from these projects (control group). In this control group we will have two major groups – clients who are still living at home and clients who are institutionalized. All clients who are in the projects and have not given their informed consent will be excluded from this database.

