**Methods/design:**

This is a longitudinal intervention study based on a quasi-experimental design. Researchers use three comparison strategies to evaluate intervention - comparison among different types of projects, comparisons between older persons in the projects and older persons not benefiting from a project but who are still at home and between older persons in the projects and older persons who are already institutionalized. Projects are asked to include clients who are frail and at risk of institutionalization. In the study we use internationally validated instruments such as the interRAI Home Care instrument, the WHO-QOL-8 and the Zarit Burden Interview-12. These instruments are filled out at baseline, at exit from the project and 6 months after baseline. Additionally, caregivers have to do a follow-up every 6 months until exit from the project. Criteria to exit the cohort will be institutionalization longer than 3 months and death. The main analysis in the study consists of the calculation of incidence rates, cumulative incidence rates and hazard rates of definitive institutionalization through survival analyses for each type of project.

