 The cognitive performance scale (CPS2) is an internationally validated scale that describes a person’s cognitive status. The scores vary from 0 to 6 and the scale consists of 5 items from the interRAI HC instrument: skills for daily decision-making, making oneself understood, short-term memory recall, procedural memory and eating impairment. Higher scores indicate a greater degree of cognitive impairment. Several studies have shown a significant correlation between the CPS scale and the Mini-Mental State Examination (MMSE) [38-41].

 – Research question 4 - Which types of projects are associated with a decreased risk of institutionalization of frail older persons?

In order to answer the fourth research question, the definitive institutionalization (more than 90 consecutive days in residential care) will be used as event. The analysis consists of the calculation of incidence rates, cumulative incidence and hazard rates of definitive institutionalization through survival analyses for each type of project. Survival analysis measures the time to a certain event or change of state, in this case, institutionalization. The multivariate Cox model which will be calculated from this analysis will allow us to isolate the effects of the intervention from the effects of confounding variables. These variables are extraneous variables which correlate (positively or negatively) with both the dependent variable and the independent variable. In this analysis we will use the variables of Table 2 as confounding variables. The use of a Cox model may improve the estimate of the intervention effect by narrowing the confidence interval. Another important advantage of this analysis is that it takes into account the variability of covariates across time which makes it very appropriate for longitudinal studies [42-44].

 – Research question 5 - Is the interRAI Maple scale a good predictor of institutionalization in our study?

The fifth research question will be approached by using a multiple logistic regression model with the Methods for Assigning Priority Levels scale (Maple) as one of the independent variables. This interRAI scale is known to be a predictor for institutionalization and can be used as an indicator for allocation of home care resources and prioritization of clients needing community or residential care. MAPLe is an internationally validated predictor of nursing home placements, caregiver distress and ratings that the client would be better off elsewhere [45].

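### Ending follow-up at project exit can censor clients before the 90-day institutionalization event is reached, and that censoring is plausibly related to risk

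*Protocol article*

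**What the plan says.** The abstract (Methods/design) and the Data collection section of the protocol article both name two exits: "Criteria to exit the cohort will be institutionalization longer than 3 months and death". Data collection then adds a third end point for observation, which the abstract does not carry: "Follow up will also end for clients who leave the projects".

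The same section describes the repeat assessments: "caregivers have to do a follow-up every 6 months until the moment clients leave the project". It dates the observation period, "Follow-up of clients happens from March 2011 until July 2013", and gives its length per client, "A client follow-up period will vary between 6 to 36 months".

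Under Analyses, research question 4, "the definitive institutionalization (more than 90 consecutive days in residential care) will be used as event". The analysis is the "calculation of incidence rates, cumulative incidence and hazard rates of definitive institutionalization through survival analyses for each type of project", with a multivariable Cox model that adjusts for the variables of Table 2.

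Data collection also plans to link the clients' interRAI data to the national IMA database and to add the IMA data to their analysis. The IMA control group is to be divided into people living at home and people in an institution. The article does not say that IMA supplies institutionalization events for project clients after they have left a project.

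**The concern.** The event takes more than 90 days to be reached, but observation may stop earlier, on the day the client leaves the project. The projects support people at home (night care, occupational therapy and so on). Leaving because home care no longer suffices, or because of an admission, is plausibly tied to the outcome. A Cox model needs censoring to be uninformative given its covariates. Adjusting for Table 2 cannot bring back an event that was lost because the admission itself ended participation.

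Research question 4 carries the study's main goal, which is to find the project types that best delay institutionalization. If admitted clients drop out of view, the rates for every type are too low. If they drop out more in some types than in others, the comparison between types partly reflects how files are closed rather than how well the project works.

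**Working it through.** **1. The plan's own figure.** The only calculation given is the sample size: 75 per group for effect size 0.50, two-sided 0.05 and power 85%. A two-sample t-test gives 73 (normal approximation 72), and power at 75 is 86.0%, so the figure reproduces. It contains no event rate, hazard ratio or loss to follow-up, and so does not bear on this point.

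**2. The rules side by side.**
- The event requires an uninterrupted residential stay of over 90 days (Analyses, research question 4).
- Follow-up ends at project exit (Data collection).
- A client who leaves before admission, or between day 1 and day 90 of the stay, therefore has no observed event under the literal rule.
- A client who is admitted and remains in the project past day 90 does have one.
- The text does not say which of these happens on admission.
- The 6-month minimum follow-up also sits badly with the exit rule. Repeat assessments are conditional on staying in the project beyond 6 months, which implies that some clients stay less.

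**3. Size on the hazard-ratio scale.** The article gives no admission rates, exit rates or stay lengths by type, so the shares below are assumptions. Let q be the share of admissions at which project participation, and hence follow-up, ends. The recorded hazard is then about (1 − q) times the true one. With a true hazard ratio of 1 between types A and B, the recorded ratio (B vs A) is about (1 − qB)/(1 − qA):

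| qA | qB | Recorded hazard ratio |
|---|---|---|
| 0.25 | 0.25 | 0.75/0.75 = 1.00 |
| 0.10 | 0.30 | 0.70/0.90 = 0.78 |
| 0.20 | 0.50 | 0.50/0.80 = 0.63 |

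**4. Size on the absolute scale.** I simulated a window of 28 months (about March 2011 to July 2013), at least 6 months of potential follow-up, and the event 3 months after admission. Deaths were assumed at 15% per year and admissions at 10%, 20% or 30% per year. With no other exits, q = 0.2, 0.5 and 0.8 left 80%, 50% and 20% of qualifying events counted. If a further 30% per year left for unrelated reasons, 59–60%, about 37% and 15% were counted.

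The kind of exit matters. At 20% admissions per year:
- unrelated exits alone (30% per year) moved the event rate only from 0.174 to 0.164 per person-year, because more of the observed time falls in the early months when no event is yet possible;
- q = 0.5 with no other exits moved it from 0.174 to 0.090.

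**5. Consequence for testing.** A spurious hazard ratio of 0.63 (0.625 unrounded) would be declared significant at two-sided 0.05 with probability Φ(|ln 0.625| × √d / 2 − 1.96), with d total events split 1:1. With |ln 0.625| = 0.470, this is 0.38 at 50 events, 0.65 at 100 and 0.82 at 150.

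**The case against.** A reader might infer that institutionalizations are in fact lost, and by different amounts in the different project types. The documents do not support that. Nowhere is admission equated with leaving the project. The cohort-exit criterion of over three months in an institution points the other way, since it implies that an admitted client can stay in the cohort until the event is reached. There are no exit rates or stay lengths by type, and with equal losses the hazard ratio between types stays at about 1. The article also gives no follow-up rule for the IMA controls, so a contrast with them on this point cannot be asserted.

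Three further defences deserve weight.
- **Follow-up may mean questionnaires only.** The section does use the word that way for the six-monthly assessments. But the exit sentence comes directly after the cohort-exit criteria and shortly after a dated period of client follow-up, so this reading is not secure.
- **The IMA linkage could recover the events.** It could, and a condensed article need not spell out every data source. But the article states a rule that ends follow-up and nowhere commits to looking for events beyond it. The linkage shows that a repair is feasible, not that one is planned.
- **Covariate adjustment helps.** Table 2 includes function, cognition and caregiver burden, assessments are also made at exit, and the article mentions covariates that vary over time. This may account for part of the exit due to gradual decline. It does nothing for losses caused by the admission itself.

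The abstract's silence on the third rule is ordinary condensation and carries no weight.

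**Conclusion.** The concern stands as a conflict between a stated follow-up rule and the event definition for the main research question. Taken literally, clients who leave before admission or within the 90 days cannot be counted, and the reason for leaving is plausibly related to risk. Incidence rates and cumulative incidence by type would then be too low. Bias in the hazard ratios between types is a risk rather than an established fact: it requires exit practice to differ between types. Under assumed shares and a true ratio of 1, it ranges from none (equal losses) through 0.78 (10% vs 30%) to 0.63 (20% vs 50%). Exits unrelated to risk cost events and precision but would not by themselves bias the hazard. The point is worth correcting because it touches the main goal and the remedy is cheap.

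**What to change.** State in Data collection that project exit ends the questionnaires only, and say whether admission to residential care counts as leaving the project. Then:

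- Ascertain institutionalization for every consenting client from inclusion to one common closing date through the IMA linkage already planned, whether or not the client is still in the project. IMA is already meant to separate controls at home from those in an institution.
- Ascertain death in the same way if IMA or another linked source records it. The article does not show that IMA does, so this needs checking.
- Analyse by project type at inclusion.
- Allow for the confirmation window: either read the data for 90 days past the closing date, or set the closing date 90 days before the last available data.
- Keep censoring at project exit as a sensitivity analysis.

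The cost is a change of wording and some extra data extraction. The estimate also changes meaning: it becomes the effect of having been enrolled in a project type rather than of remaining in it, and the article should say so.

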### Analyses

 – Research question 1 - Do characteristics of populations differ across projects?

In order to answer this first research question comparisons will be made between the populations in the different types of projects to explore whether they present particular characteristics. In these comparisons we will use the variables shown in Table 2 Frequencies will be calculated for categorical variables and means and medians with confidence intervals for continuous variables. Other possible comparison will be done by analysis of variance. All the statistical analysis in the study will be performed with the software Stata 11.1.

 – Research question 2 - Which types of projects are associated with less decline of the functional and cognitive performance of frail older persons?

 – Research question 3 - Which types of projects contribute to a better quality of life of frail older persons?

**Table 2 T2:** Variables to characterize the population of the study

**Topic**	**Variable**	**Source**	**Type of variable**
General information	Civil status	InterRAI HC	Qualitative
	Age	InterRAI HC and IMA	Continuous
	Gender	InterRAI HC and IMA	Dichotomic
Quality of Life	WHOQOL items score	WHOQOL-8	Continuous
Socio-economic status	Financial difficulties	InterRAI HC	Dichotomic
Primary caregiver’s burden	Zarit Burden score	ZBI-12	Continuous
Functional status	Katz score	IMA	Qualitative
	interRAI ADL hierarchy scale	InterRAI HC	Ordinal (0 to 6)
	interRAI IADL scales	InterRAI HC	Ordinal (0 to 48)
	interRAI Communication scale	InterRAI HC	Ordinal (0 to 8)
	interRAI CPS2 scale	InterRAI HC	Ordinal (0 to 6)
	interRAI DRS scale	InterRAI HC	Ordinal (0-14)

Longitudinal analyses will be performed to answer the second and third research questions. Outcome variables will be the interRAI ADL hierarchy scale, the interRAI CPS2 scale and the WHOQOL scale. Mean will be compared between arms of the study and covariate analysis (ANCOVA) will be done to control results for potentially confounding variables.

 The ADL hierarchy scale is a measure of a person’s functional performance. It is based on the concept of early, middle and late loss of ADLs and consists of 4 items from the interRAI instruments: personal hygiene, toilet use, locomotion and eating. The scores vary from 0 to 6 and the higher the score, the greater the dependency [36,37].

 The cognitive performance scale (CPS2) is an internationally validated scale that describes a person’s cognitive status. The scores vary from 0 to 6 and the scale consists of 5 items from the interRAI HC instrument: skills for daily decision-making, making oneself understood, short-term memory recall, procedural memory and eating impairment. Higher scores indicate a greater degree of cognitive impairment. Several studies have shown a significant correlation between the CPS scale and the Mini-Mental State Examination (MMSE) [38-41].

 – Research question 4 - Which types of projects are associated with a decreased risk of institutionalization of frail older persons?

In order to answer the fourth research question, the definitive institutionalization (more than 90 consecutive days in residential care) will be used as event. The analysis consists of the calculation of incidence rates, cumulative incidence and hazard rates of definitive institutionalization through survival analyses for each type of project. Survival analysis measures the time to a certain event or change of state, in this case, institutionalization. The multivariate Cox model which will be calculated from this analysis will allow us to isolate the effects of the intervention from the effects of confounding variables. These variables are extraneous variables which correlate (positively or negatively) with both the dependent variable and the independent variable. In this analysis we will use the variables of Table 2 as confounding variables. The use of a Cox model may improve the estimate of the intervention effect by narrowing the confidence interval. Another important advantage of this analysis is that it takes into account the variability of covariates across time which makes it very appropriate for longitudinal studies [42-44].

 – Research question 5 - Is the interRAI Maple scale a good predictor of institutionalization in our study?

The fifth research question will be approached by using a multiple logistic regression model with the Methods for Assigning Priority Levels scale (Maple) as one of the independent variables. This interRAI scale is known to be a predictor for institutionalization and can be used as an indicator for allocation of home care resources and prioritization of clients needing community or residential care. MAPLe is an internationally validated predictor of nursing home placements, caregiver distress and ratings that the client would be better off elsewhere [45].

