### Sample size considerations

Beneficiaries will be grouped by type of projects as shown in Table 1 in order to get a reasonable sample size for each side of the comparison. Using an effect size of 0.50, a two-sided significance level of 0.05 and a power of 85%, 75 participants are needed in each group. We expect each project to include at least 45 participants per year because this is the minimum size of case load projects reported at the beginning of their activities. The clusters of projects will have then a larger sample size than indicated by the sample size calculation.

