### Study population

The study will include older people receiving home care services who are at least 65 years old. Projects are asked to include only clients who are frail and at risk of institutionalization. Due to practical reasons, frailty is measured in the study with two different scales and caregivers are allowed to choose between them. One of these scales is the Edmonton Frail Scale [17,18] with a cutoff point of 6. Another scale is an adapted version of the Katz scale for Belgian home care and residential care [19]. Older people with a Katz score equal to A, B or C will be included [20]. Clients who have been diagnosed with dementia by a geriatrician, neurologist or psychiatrist may also be included in the study.

Each project has to collect data on at least 75% of their total client population in order to ensure representativeness. This means that caregivers have to complete questionnaires for at least 75% of clients benefiting from their projects.

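### Means for function, cognition and quality of life can describe only surviving clients, so a project type with more deaths can look better on decline

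*Protocol article*

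**What the plan says.** The Analyses section of the protocol article names the outcomes for research questions 2 and 3: "Outcome variables will be the interRAI ADL hierarchy scale, the interRAI CPS2 scale and the WHOQOL scale". It announces longitudinal analyses and then gives the method: "Mean will be compared between arms of the study and covariate analysis (ANCOVA) will be done to control results for potentially confounding variables".

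Data collection has the questionnaires completed "at inclusion of the frail older person in the project (baseline), at exit from the project and 6 months after baseline", and every 6 months after that while the client stays in the project. The same section says: "Criteria to exit the cohort will be institutionalization longer than 3 months and death". It also says that professional caregivers complete the interRAI HC, the source of both ADL hierarchy and CPS2, from observation and from interview of the older person and the main informal caregiver. The WHO-QOL-8 section says that the client must complete that scale personally.

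On the population, the article says: "Projects are asked to include only clients who are frail and at risk of institutionalization". Stated follow-up is 6 to 36 months. Neither the Analyses section nor the limitations in the Discussion say how a client who dies enters the comparison for research questions 2 and 3.

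**The concern.** An assessment is due at exit, and death is an exit at which the assessment cannot be made as described. A client who dies before month 6 contributes no follow-up score. One who dies later keeps the earlier scores but has none for the last stretch of decline. The stated means can therefore be formed only from clients who were alive to be scored.

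This differs from an ordinary missing visit. A score after death does not exist, so whether death counts as decline is part of what the question asks. Fixed time points, a mixed model or imputation would not settle it.

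Project types are not randomised and serve different needs, and research question 1 itself asks whether their populations differ. Unequal mortality is therefore plausible. If clients who decline faster are also likelier to die, losing them flatters the type that loses more. Readers who use the results to choose project types could then credit one with preserving function partly because more of its clients died.

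**Working it through.** **The plan's own figure.** Sample size considerations states: "Using an effect size of 0.50, a two-sided significance level of 0.05 and a power of 85%, 75 participants are needed in each group".
- Normal approximation: n = 2(1.960 + 1.036)² / 0.50² = 71.8, so 72 per group.
- Two-sided t-test: 72.8, so 73 per group. Power at 75 per group is about 86.5%.

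The figure of 75 is sound and not in dispute. It serves here as a yardstick: the study is sized for a difference of 0.50 SD.

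**Inputs not in the document (assumptions).** Mortality before the score compared: 10% in one type, 20% or 30% in the other. True decline is the same in both types, so any difference among survivors is spurious.

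**Model 1: frailty drives both decline and death.** Change = 0.5 + 0.7 × frailty + N(0, 0.8), with frailty standard normal. The SD of change is √(0.49 + 0.64) = 1.06. The log-odds of death rise by 1.0 per SD of frailty. Simulated results:

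| Mortality | Mean decline, survivors | Decline ≥1, survivors | Decline ≥1, all clients | Decline ≥1 or death |
|---|---|---|---|---|
| 10% | 0.44 | 30% | 32% | 37% |
| 20% | 0.38 | 27-28% | 32% | 42% |
| 30% | 0.32 | 26% | 32% | 48% |

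The spurious advantage of the higher-mortality type is 0.44 - 0.38 = 0.06 points, or 0.44 - 0.32, which is 0.11 points before rounding. In SD units that is about 0.05-0.11, or 10-22% of 0.50.

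**Allowing for the planned adjustment.** The article does not list the ANCOVA covariates, but Table 2 includes baseline measures related to frailty. The same model with a baseline covariate that explains part of the frailty variance gives:

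| Frailty variance explained | 10% v 20% | 10% v 30% |
|---|---|---|
| none | 0.06 | 0.11 |
| 25% | 0.045 | 0.09 |
| 50% | 0.03 | 0.06 |
| 75% | 0.02 | 0.03 |

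Adjustment shrinks the bias but does not remove it unless the covariates capture all of the link between death and decline.

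**Model 2: a check by a different route.** Change has SD 1 and mean 0.5. Death occurs when a liability correlated ρ with decline exceeds h = z(1-d), where d is mortality. Then survivor mean = 0.5 - ρ φ(h)/(1-d), and φ(h)/(1-d) is 0.195, 0.350 and 0.497 for d = 10%, 20% and 30%.
- ρ = 0.3: advantage 0.05 SD (10% v 20%) or 0.09 SD (10% v 30%).
- ρ = 0.5: 0.08 or 0.15 SD.
- ρ = 0.7: 0.11 or 0.21 SD.
- ρ = 0, or equal mortality: zero.

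A simulated ANCOVA on baseline score gave the same contrasts, because in this model the selection acts on decline after baseline and not on the baseline score.

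**Against the expected sample.** The article says: "We expect each project to include at least 45 participants per year". Eight case-management projects then give 8 × 45 = 360 clients in a year. In Model 2 with ρ = 0.5 and 360 recruited in each of two types, the chance of a significant result favouring the higher-mortality type is about 17% (10% v 20%) or 47% (10% v 30%), against a nominal 2.5%. This is an upper illustration: it has no covariate related to decline and ignores clustering by project.

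**The case against.** The strongest reply is that a condensed article gives these two questions only a few sentences. It fixes no time point, model or analysis set, and never says that deaths are dropped or that the analysis is complete-case. That is right, and a reader should not infer such a rule. What stands is narrower: on the instruments as described no score follows death, so a mean of scores is a mean over survivors whatever a fuller plan says about missing visits. For ADL hierarchy and CPS2 this is a strong inference, since a retrospective caregiver rating is neither described nor excluded. For the WHO-QOL-8 it follows directly from self-report.

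Second, the size is uncertain and probably modest. The quoted method includes covariate adjustment, which lowers the illustrative figures, and the document gives no reason to expect a two- to threefold difference in mortality. Both objections stand and are reflected in the range given.

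Third, a reader might infer that the ranking of project types reverses, because decline or death is 42-48% in the higher-mortality type against 37%. The calculation does not support that as a statement about decline: true decline of at least 1 point is 32% in both types by construction. The composite differs because it counts deaths. For the same reason, requiring the composite to agree before a type is credited with less decline would let mortality differences between non-randomised groups overrule a functional result. The document gives no ground for that.

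Fourth, the main goal is delaying institutionalization (research question 4), and this point does not touch that analysis.

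**Conclusion.** The point holds in a limited form. As written, the comparison for research questions 2 and 3 describes clients alive at the assessment, while the questions refer to frail older persons without that restriction. It can favour a non-randomised type with more deaths. Two conditions are needed: mortality must differ between types, and death must be linked to decline that the covariates do not capture. Both are plausible in a frail cohort followed for up to 36 months, but the document quantifies neither. Under the assumed mortality the bias is about 0.06-0.11 points unadjusted and 0.02-0.09 points with partial adjustment, on scales running from 0 to 6. That is small beside the 0.50 SD planning effect, but it is systematic and a larger sample does not reduce it. The documents do not show that any ranking is wrong, only that the stated analysis could not reveal it. The change is worth making; the point does not invalidate the design.

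**What to change.** In Analyses, under research questions 2 and 3:
1. Keep the ANCOVA, and state that its ADL hierarchy, CPS2 and WHOQOL results apply to clients alive at the assessment.
2. Show the number and percentage of deaths by project type beside each mean.
3. For ADL hierarchy and CPS2, add a supplementary ordinal comparison at months 6 and 12, adjusted for the same covariates, with death as a category worse than a score of 6. Present it as a sensitivity analysis of decline or death, not as a veto on the functional result.

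The cost is one extra model per scale. Death is already a cohort exit and the 6-monthly visits are already planned, so no new instrument or visit is needed. There are two limits. The composite mixes survival with function, which is why it stands beside the ANCOVA and does not replace it. Follow-up also ends for clients who leave a project, so deaths after leaving may not be recorded; clients who left alive should be treated as missing and not counted as deaths.
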